#### 2.5.2. Data Monitoring

The Data and Safety Monitoring Board (DSMB) of the Clinical Research Center in Changhai Hospital, which is made up of independent clinical specialists and statisticians with access to unblinded data, will monitor the study’s safety. Performance and safety of the study will be reviewed monthly by the DSMB, which is separate from the investigational site, the sponsor, and any conflicting interests. The criteria for terminating the study for a given trial participant have been described previously. The allocated intervention for participants will be revealed by the DSMB, which will also make the final decision to end the study.

The complete, anonymous final data set will be accessible to the data manager in Changhai Hospital’s Clinical Research Center. Others will have access to the final data set following the approval of the DSMB in the Clinical Research Center.

#### 2.5.3. Confidentiality

The PI will obtain all personal information and sign a confidential disclosure agreement before the trial. Each participant will be given a special research identifier to decrease the probability of accidental disclosure of identifiable data during the study. The printed materials will be secured in a locked cabinet, which is locked in the research office, and the electronic data will also be stored in a passcode-protected database in order to protect confidentiality. Access to personal data will be limited by the specific privilege assignments in the trial. Any information and documents used for assessment or statistical analyses will be represented by code.

#### 2.5.4. Statistical Analysis

Masked statistical analysts will conduct the analyses at the Clinical Research Center of Changhai Hospital. The full analysis set including all randomized patients and per protocol set, including patients with the primary outcome, will be performed. Safety and efficacy analyses will be conducted based on the intention-to-treat analysis population, which includes all randomized patients. Missing data will be handled using the mixed model for repeated measurements.

All statistical analysis will be performed by SPSS 23.0 statistical analysis software (IBM SPSS, Armonk, NY, USA). Continuous variables in normally distributed data represented as mean (SD) will be compared using the Student’s t-test, while continuous variables in non-normal distribution data reported as medians (quartiles) will be compared using Mann-Whitney *u* test. Categorical variables described as frequency and percentages will be compared using χ^2^ test or Fisher’s exact test. *p* < 0.05 will be regarded as statistically significant.

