#### 2.1.2. Secondary Outcomes

The scores of QoR-15 at 72 h and 1 month after surgery.The NRS scores before discharge from PACU at 24 h, 72 h, and 1 month after surgery; rescue analgesics; nausea and vomiting 24 h after surgery; remifentanil consumption during operation; emergence agitation; PACU LOS; and SNB-related adverse events.The duration of anesthesia and surgery, time to respiratory recovery, time to response, and time to extubation.

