#### 2.1.4. Sample Size and Recruitment

The study’s primary outcome is the scores of QoR-15 at 24 h after surgery. Our preliminary study showed that the scores of QoR-15 at 24 h following DBS operation in PD patients without nerve block were equivalent to 110 (10.1). A previous study has shown that the QoR-15 score change of 8 points was deemed to be a clinically significant difference [26]. We calculated the required number of patients using PASS 11 software (NCSS, Kaysville, UT, USA) with an alpha error of 0.05 and power 95% (test for two proportions, two-sided *t*-test), and determined that 35 patients would need to be included in each group. Considering a 20% dropout rate, we defined a sample size of 88 participants.

Recruitment will be performed during a 12-month period. The study will end when the last patient enrolled undergoes an assessment of QoR 1 month after surgery. The protocol has been initiated as planned in April 2022 and will be completed in March 2023.

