### 2.3. Interventional Methods

#### 2.3.1. Intervention

Participants randomized to the SNB group will receive general anesthesia combined with SNB and ICNB using 0.5% ropivacaine, which will be performed exclusively by an attending anesthesiologist. Meanwhile, patients in the control group will receive general anesthesia without the nerve blocks. An attending anesthesiologist will select the sites of the nerve blocks based on the surgical incision site. After negative aspiration, the scalp nerve will be blocked, including the greater occipital nerve (2–3 mL), superficial temporal nerve (2–3 mL), trochlear nerve (2–3 mL), and supraorbital nerve (2–3 mL). The total volume in SNB will not exceed 10 mL.

Ultrasound-guided unilateral ICNB will be conducted at the plane of T4–T5 next to the sternum in patients who are in the supine position. A longitudinally oriented, linear ultrasonic probe will be used to determine the pleura, internal intercostal muscles, rib, and innermost intercostal muscles. An echogenic needle will be inserted using an in-plane technique to target the inferior margin of rib. A volume of 10–15 mL with 0.5% ropivacaine will be injected into the intercostal spaces where the incision locates after negative aspiration. ICNB is considered successful when pleural movement is observed in intercostal spaces.

The block efficacy for formal dermatomal sensory will not be formally tested because patients under general anesthesia are unconscious. The anesthesiologist performing the nerve blocks will not visit patients in the perioperative period. After the nerve blocks, the anesthesiologist will cover the dressing at the relevant areas to hide the allocation. Only the dressing will be covered in the same site of the control group without injecting normal saline, in consideration of ethical care.

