#### 2.3.4. Adverse Event

All AEs will be recorded through the symptoms reported by the patients at each visit. Nerve-block-related AEs might include hematoma and infection in the block site, and pneumothorax and local anesthetic toxicity. If a patient is suspected to be affected by local anesthetic poisoning, an immediate stop to the nerve blocks and an active rescue treatment will be administered.

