### 2.4. Randomization and Blinding

Patients will be randomly assigned to the SNB group and control group in a ratio of 1:1 using random number tables generated by a computer, including numbers 1–88 which is performed by an anesthesia nurse. The patients corresponding to the first 44 random numbers will be assigned to the control group, while the rest will be allocated to the SNB group. An anesthesia nurse with no direct clinical role in the trial will type the group assignment on separate papers, fold them up, and put them inside sequentially numbered sealed opaque envelopes.

Attending anesthesiologists who are not involved in the follow-up will perform SNB combined with ICNB after the induction of general anesthesia. Participants will be informed as to whether they will receive nerve blocks or not by the research coordinator, who will not participate in treatment or evaluation. Therefore, the attending anesthesiologists, research coordinator, and anesthesia nurse will know the allocation schedule. Group assignment will be concealed from patients, anesthesiologists responsible for operation, and investigators who are in charge of assessing and collecting data. Group allocation will not be disclosed until all data collection is completed. After consultation with the principal investigator (PI), the blinding will be removed if a concern regarding local anesthetic toxicity arises.

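### Safety is analysed in all randomised patients by intention to treat, so block-related adverse event rates would be diluted or misplaced if any patient did not receive the assigned treatment

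*Protocol article*

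**What the plan says.** Section 2.5.4 (Statistical Analysis) fixes the safety population explicitly: "Safety and efficacy analyses will be conducted based on the intention-to-treat analysis population, which includes all randomized patients". The same section names two other sets: "The full analysis set including all randomized patients and per protocol set, including patients with the primary outcome, will be performed". The first is again everyone randomised. The second is defined by having the primary outcome, not by what was administered. The article defines no safety set and no analysis by treatment received.

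Section 2.1.2 lists "SNB-related adverse events" among the secondary outcomes, and section 2.3.4 gives examples: "Nerve-block-related AEs might include hematoma and infection in the block site, and pneumothorax and local anesthetic toxicity".

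On exposure, section 2.4 says that the attending anesthesiologists "will perform SNB combined with ICNB after the induction of general anesthesia", and Table 1 places allocation before induction. Controls get no injection at all: "Only the dressing will be covered in the same site of the control group without injecting normal saline" (section 2.3.1).

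**The concern.** Analysis by randomised group is the cautious choice for a superiority comparison of efficacy, because patients who do not get their assigned treatment pull the groups together. For harms, the same pull makes the intervention look safer.

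Here the harms of interest depend on an injection, and assignment comes before it. A patient allocated to SNB whose operation is cancelled, or whose block is omitted, enlarges the SNB denominator without having been at risk. A control patient blocked by mistake who then had a complication would be tabulated as a control event. Section 2.5.4 states the rule outright, so this is not a detail left to an unseen analysis plan. What is at stake is the accuracy of a few descriptive rates for rare events with 44 patients per group.

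**Working it through.** **Inputs from the protocol article**
- 88 patients, allocated "in a ratio of 1:1 using random number tables generated by a computer". Section 2.4 gives the first 44 numbers to control, which leaves 44 for SNB.
- Safety population: all randomised (2.5.4). I read intention to treat in its ordinary sense, by assigned group.
- Controls receive a dressing and no injection (2.3.1), so correctly treated controls have no block-caused events.

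**Inputs the article does not give, assumed here**
- The number of SNB patients not blocked, *u*: 0, 1 or 2.
- The number of block-related events: 0 or 3, for illustration.
- The one-sided 95% upper bound as the summary when no event is seen.

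The article has no safety rate or bound of its own to reproduce.

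**1. Direction.** Let *r* be the event rate among blocked patients and *q* the share of the SNB group not blocked.
- As-randomised SNB rate = *r* × (1 − *q*).
- If the same share *q* of controls is blocked, the as-randomised control rate = *r* × *q*.
- The difference is then *r* × (1 − *q*) − *r* × *q* = *r* × (1 − 2*q*).

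Both factors are at most 1, and both equal 1 at *q* = 0.

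**2. Three events among blocked SNB patients**

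| Not blocked | As randomised | By treatment received |
|---|---|---|
| 0 | 3/44 = 6.8% | 3/44 = 6.8% |
| 1 | 3/44 = 6.8% | 3/43 = 7.0% |
| 2 | 3/44 = 6.8% | 3/42 = 7.1% |

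**3. No events.** Upper bound = 1 − 0.05^(1/n).
- n = 44: 6.6% (as randomised, whatever *u* is).
- n = 43: 6.7%.
- n = 42: 6.9%.

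The shift is about 0.1 to 0.3 percentage points.

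**4. One control blocked in error who has the only event.** Everyone else is treated as assigned.
- As randomised: SNB 0/44 = 0%, control 1/44 = 2.3%.
- By treatment received: blocked 1/45 = 2.2%, not blocked 0/43 = 0%.

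A single misplaced event reverses the table. This is the only scenario of the three in which the result changes in kind, and it needs both a protocol deviation and a complication.

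**5. Is the 20% dropout a bound for *q*?** No. Section 2.1.4 uses it to inflate the sample for QoR-15 at 24 h after surgery. The block is a single procedure given after induction. A patient lost after that has been exposed and belongs in the safety denominator under either rule.

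**6. Stopped blocks.** Section 2.3.4 foresees halting the blocks when local anesthetic toxicity is suspected. Such a patient has already been exposed. A grouping by completed block could move a toxicity case to the unblocked group, which would be worse than the present rule.

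**The case against.** The strongest reply is that departures from assignment should be rare. The block is one in-theatre procedure, performed by an anesthesiologist who knows the allocation, and no section provides for blocking a control. The interval between allocation and induction is not given, so the scope for cancelled surgery is unknown. With complete receipt the two analyses are identical. The article states no safety hypothesis or margin, so the block-related events are in effect descriptive counts in the SNB group. An unblocked SNB patient alters the denominator but removes no event. The monitoring board reviews safety monthly with access to unblinded data (2.5.2), so patient protection during the trial does not depend on this table. Analysis as randomised also preserves the randomised comparison.

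Most of this stands, and it limits the size of the point. It does not remove the point. The stated rule has no provision for a mismatch between assignment and exposure, and the direction of the error is known.

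A reader might infer that the plan will understate block harms by up to a fifth, taking the 20% dropout allowance as the share not blocked. The documents do not support that: the allowance concerns the 24 h outcome, and nothing suggests that so many patients would go unblocked. A reader might also count abandoned blocks as unexposed. Section 2.3.4 points the other way.

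**Conclusion.** The point holds in conditional form. If any randomised patient does not receive the assigned treatment, the rule in section 2.5.4 either dilutes the block-related event rate in the SNB group or places an event in the wrong group, and both are anti-conservative for harms. With full receipt there is no effect. With one or two unblocked patients, the zero-event bound moves from 6.6% to 6.7% or 6.9%. This rests on 44 patients per group, on the ordinary reading of intention to treat, and on assumed numbers of unblocked patients and events, because the article gives neither a non-receipt rate nor an adverse event rate. The article does not show that dilution will occur. This is a cheap improvement of minor weight.

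**What to change.** In section 2.5.4, keep all randomised patients for efficacy and add a sentence for safety along these lines: adverse events will be analysed in patients who received study anesthesia, grouped by treatment actually received; any patient in whom a block injection was started, including one stopped for suspected toxicity, counts as exposed; a table by randomised group is given as a supplement.

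The cost is that sentence, one exposure flag in the data set, and a second denominator in the safety table, which readers will need to have explained. No extra patients, visits or changes to care are needed. If every patient is treated as assigned, the two tables agree.

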#### 2.1.3. Outcome Measures

The QoR-15 questionnaire will be used to measure the patients’ quality of recovery at 24 h, 72 h, and 1 month after operation. A higher QoR-15 score (from 0 to 150) suggests greater recovery after surgery. The NRS score will be used to measure postoperative pain, and a higher score indicates more severe pain after surgery. The NRS scores will be recorded before discharge from PACU at 24 h, 72 h, and 1 month following surgery. Neuropathic pain will be assessed before surgery by a modified Douleur Neuropathique 4 (DN4) questionnaire on a scale of 0–10. A total DN4 score of more than or equal to 4 indicates neuropathic pain.

Emergence agitation is identified as improper behavior that presents itself as excitation, agitation, and concurrent orientation disorder during the anesthesia recovery phase. Respiratory recovery time refers to the interval between the end of anesthetic drugs and respiratory recovery. Response time is defined as the interval between the cessation of anesthetic drugs and response to a verbal command. Duration of time between the cessation of anesthetic drugs and extubation is referred to as the extubation time.

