#### 2.3.2. Criteria for Termination or Adjusting the Assigned Interventions

There will be no unique criteria for changing assigned interventions, but there are situations under which the research will be terminated: (1) postoperative surgical site bleeding; (2) serious DBS surgery-related complications (such as pulmonary aspiration, wound infection, respiratory insufficiency, and delirium) and nerve-block-related AEs (such as pneumothorax and local anesthetic toxicity); (3) unexpected postoperative continuation of intubation; and (4) unanticipated reoperation 24 h following surgery.

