### 2.5. Data Collection and Analysis

#### 2.5.1. Data Collection and Management

Researchers will explain the advantages of participating in the study to participants and their authorized surrogates before DBS surgery. A specific masked researcher will collect the patients’ basic characteristics before surgery. After the surgery, the blinded investigator will conduct a follow-up to record QoR-15 scores at 24 h and 72 h after surgery in the ward, and at 1 month after surgery in the outpatient clinic. Participants will be excluded if they are unable to complete the primary outcome measure. The anesthesiologists in charge will record the patients’ intraoperative data. Other data on secondary outcomes will be collected by a blinded investigator. The data collected will be first completed on a paper Case Report Form (CRF). Following this, the data manager will merge the double data into an electric database which will be examined by two inspectors.

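### The efficacy result is described as covering all randomised patients, but under every reading of the plan a patient with no QoR-15 score drops out of the primary comparison

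*Protocol article*

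**What the plan says.** The primary endpoint is a single time point: "The study’s primary outcome is the scores of QoR-15 at 24 h after surgery" (section 2.1.4). The instrument is scheduled only after the operation: "The QoR-15 questionnaire will be used to measure the patients’ quality of recovery at 24 h, 72 h, and 1 month after operation" (section 2.1.3). Table 1 agrees, with no pre-operative QoR-15.

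On the analysis population, section 2.5.4 states: "Safety and efficacy analyses will be conducted based on the intention-to-treat analysis population, which includes all randomized patients". On incomplete data it states: "Missing data will be handled using the mixed model for repeated measurements". The same section defines the per-protocol set by possession of the primary outcome, so the full set is meant to hold patients who lack it. It then names Student's t-test or the Mann-Whitney test for continuous variables, without saying how these relate to the mixed model.

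Two other sections remove patients. Section 2.5.1 states: "Participants will be excluded if they are unable to complete the primary outcome measure". Section 2.3.2 lists situations in which the research is terminated: bleeding, serious complications including delirium, nerve-block events such as pneumothorax and local anaesthetic toxicity, and "unexpected postoperative continuation of intubation; and (4) unanticipated reoperation 24 h following surgery". Section 2.5.2 refers back to these as criteria that apply to a given participant. The article does not say whether QoR-15 is still collected afterwards.

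**The concern.** Sections 2.5.1 and 2.5.4 cannot both be followed. One takes patients without the primary measurement out; the other says efficacy covers everyone randomised. The mixed model looks as if it bridges the gap, but it can do so only for patients with at least one QoR-15 score.

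The losses are unlikely to be random. The events in section 2.3.2 go with poor recovery, which is what QoR-15 measures. Some of them, the block complications, can arise in only one arm, because controls receive a dressing and no injection (section 2.3.1). A comparison of those able to answer, reported as intention-to-treat, could leave out the worst recoveries, possibly in unequal numbers. Serious events lost from the block arm would make the block look better than it is; losses from the control arm would make it look worse.

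**Working it through.** **Inputs from the article.** SD 10.1 and an 8-point target difference (2.1.4); 35 patients per group before dropout, 20% dropout, 88 in total (2.1.4); 1:1 allocation, 44 per group (2.4); QoR-15 at three post-operative visits (2.1.3, Table 1).

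**The plan's dropout step reproduces.** 70 / 0.8 = 87.5, rounded up to 88, or 44 per group. The plan thus allows for 44 − 35 = 9 losses per group. The 35 is taken as given here.

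**Step 1: what each reading does with a patient who lacks scores.**

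| Reading | No QoR-15 at any visit | 24 h missing, later score present |
|---|---|---|
| Exclusion in 2.5.1 | out | out |
| t-test or Mann-Whitney at 24 h (2.5.4) | out | out |
| Mixed model over three visits (2.5.4) | contributes nothing | enters, under missing at random |

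The first column is the same in every row.

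**Step 2: information about the 24 h difference in a mixed model.** Assume compound symmetry with correlation ρ between visits. ρ is not in the article; 0.3, 0.5 and 0.7 are used.

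- 35 complete per arm: SE = 10.1 × √(2/35) = 2.414.
- The same plus 9 per arm with no score: SE = 2.414, unchanged.
- The same plus 9 per arm missing only 24 h: SE² = 2 × 10.1² × [(1 − R²)/35 + R²/44], where R² = 2ρ²/(1 + ρ) is the share of 24 h variance explained by the two later scores. At ρ = 0.5, R² = 0.333 and SE = √(204.02 × 0.02662) = 2.331. At ρ = 0.3 and 0.7, SE = 2.380 and 2.268.
- All 44 complete: SE = 10.1 × √(2/44) = 2.153.

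The model therefore recovers something from patients who answer later and nothing from patients who never answer.

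**Step 3: would a pre-operative score have helped?** With a baseline modelled as an outcome with a common mean, the SE is 2.303, 2.091 and 1.724 at ρ = 0.3, 0.5 and 0.7. Adding 9 baseline-only patients per arm leaves each figure unchanged.

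**Step 4: size of a possible bias (illustration).** If k of 44 patients in one arm have no score and would have scored g points below those observed, the observed mean overstates that arm's mean by (k/44) × g. Neither k nor g is in the article.

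- k = 2, g = 20: 2/44 × 20 = 0.9 points
- k = 3, g = 30: 3/44 × 30 = 2.0 points
- k = 4, g = 40: 4/44 × 40 = 3.6 points

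Against the 8-point target these are 11%, 26% and 45%. With losses in both arms, the bias in the difference (block minus control) is m_B × g_B − m_C × g_C, where m is the fraction missing. If 20% of controls and 10% of the block arm are missing and g is 10 to 30 in both, it is −1 to −3 points. If m and g are equal across arms, it is 0.

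**The case against.** The strongest reply is that the loss is declared. Section 2.5.1 states the exclusion and section 2.5.4 names a set restricted to patients with the primary outcome. That is correct, and a reader who inferred that patients vanish silently would be wrong. But a declared exclusion contradicts the all-randomised population rather than excusing it.

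The second reply is that the plan never makes the mixed model the primary comparison. That also stands; calling it the primary analysis would be inference. It does not rescue the plan, because the tests that are named need a 24 h score.

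The third is that being too ill to answer at 24 h is not the same as having no QoR-15. A patient who recovers and answers at 72 h or 1 month enters the mixed model, and some listed events, such as wound infection, may come after 24 h. This stands and narrows the point. What remains for such a patient is that section 2.5.1, read literally, still excludes them, and that the model treats their unseen 24 h state as predictable from patients who could answer. That is hard to defend when the score is missing because of intubation, delirium or reoperation.

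Finally, sensitivity analyses and tables of reasons for missingness commonly belong in a statistical analysis plan. Their absence from an article is not the finding. The finding is that the published text makes a claim about its population that its own rules and methods do not deliver; the sensitivity analysis is offered as a remedy.

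**Conclusion.** The point holds in this form: sections 2.5.1 and 2.5.4 contradict each other, and under every reading patients with no QoR-15 leave the primary result although it is presented as intention-to-treat. This follows from the text and needs no assumption about event rates. It should be corrected in the analysis plan before unblinding.

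The size is not known. The 0.9 to 3.6 points rest on assumed counts, assumed shortfalls and losses confined to one arm. The plan's 20% dropout has no stated cause, so it does not show that serious events will be that frequent.

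A reader might also infer that the absence of a pre-operative QoR-15 is what causes the loss. It is not: patients with only a baseline would add nothing to the 24 h contrast either (step 3).

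**What to change.** 1. Reconcile 2.5.1 with 2.5.4: take the exclusion out of the all-randomised analysis, confine it to the per-protocol set, and continue to collect QoR-15 at later visits where possible, including after an event listed in 2.3.2.
2. State in 2.5.4 which analysis of the 24 h score is primary, and that the mixed model covers only patients with at least one QoR-15.
3. Report by arm the number of missing 24 h scores and the reason for each.
4. Prespecify one sensitivity analysis: patients without a 24 h score because of death or a serious event are ranked below all observed scores, kept in their assigned group, and compared by a rank test.

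The cost is one extra analysis and one field on the case report form for the reason. Treatment and sample size do not change. The downsides are that the sensitivity result is on a rank scale, so it gives no difference in QoR-15 points, and that it may be less favourable than the main result.

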#### 2.1.1. Primary Outcome

The study’s primary outcome is the scores of QoR-15 at 24 h after surgery.

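### The test for the primary outcome depends on the observed distribution and is not linked to the mixed model named for missing data, so the plan may yield no mean difference to set against its 8 points

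*Protocol article*

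**What the plan says.** Section 2.1.1 defines the endpoint: "The study’s primary outcome is the scores of QoR-15 at 24 h after surgery". Section 2.1.3 describes it as a score from 0 to 150, recorded at 24 h, 72 h and 1 month.

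Section 2.1.4 sizes the trial on a control value of 110 (10.1) and on the statement that a "QoR-15 score change of 8 points was deemed to be a clinically significant difference". It names a two-sided t-test, alpha 0.05 and 95% power, and arrives at 35 per group, or 88 in total after 20% dropout.

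Section 2.5.4 then says three things that bear on the primary comparison:

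- Normally distributed continuous variables are summarised as mean (SD) and compared by Student's t-test, while "continuous variables in non-normal distribution data reported as medians (quartiles) will be compared using Mann-Whitney".
- "Missing data will be handled using the mixed model for repeated measurements".
- Efficacy is analysed in the intention-to-treat population, defined as all randomised patients.

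The section gives no separate rule for the 24 h QoR-15 and does not say which of these methods supplies the primary result.

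**The concern.** The general test rule covers the primary outcome by default, so the trial's own data decide between two analyses that answer different questions. The t-test estimates a mean difference. The Mann-Whitney test, reported with medians and quartiles, does not. If the second route is taken, the report holds no estimate of the quantity on which the trial was sized.

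The mixed model adds a second uncertainty. It is a full analysis with its own 24 h estimate, interval and p-value. It does not fill in missing scores that a t-test or rank test could then use. With any missing 24 h score, a reader cannot tell whether the deciding p-value comes from the two-sample test on observed scores or from the model. The trial's conclusion could rest on either.

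**Working it through.** **1. What the trial was sized on.** Inputs from section 2.1.4: difference 8, SD 10.1, two-sided alpha 0.05, power 95%.

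- n per group = 2 × (1.960 + 1.645)² × 10.1² / 8² = 2 × 13.0 × 102.01 / 64 = 41.4, so 42 (43 with the noncentral t).
- The stated 35 per group is not reproduced. At 35 per group the power is 91.2% by the normal approximation and 90.4% by the t distribution.
- The dropout step is reproduced: 35 / (1 − 0.20) = 43.75, so 44 per group and 88 in total.

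The shortfall at 35 is a separate matter, as is the label "test for two proportions, two-sided" attached to a t-test. What matters here is that the inputs, a mean with its SD and a difference in points, describe a difference in means.

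**2. What each route in section 2.5.4 delivers for QoR-15 at 24 h.**

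| Route | Effect measure | Patient without a 24 h score |
|---|---|---|
| t-test | mean difference | dropped |
| Mann-Whitney | medians and a rank p-value | dropped |
| Mixed model, 24 h contrast | mean difference | kept if a 72 h or 1 month score exists |

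The t-test and the mixed model target the same quantity. With complete data, no covariates and an unstructured covariance they give the same estimate. Only Mann-Whitney departs from the sizing target. The two two-sample tests depart from the stated population. If the whole planned dropout fell before 24 h, 0.20 × 88 = 17.6, about 18 patients, would be affected. That is an upper bound, since loss by 24 h may well be lower.

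**3. How often the switch would occur.** The article states no normality criterion. The check assumes a Shapiro-Wilk test at 5% in each arm, with Mann-Whitney used if either arm fails, and 35 to 44 patients per arm.

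The ceiling is distant. It lies (150 − 110) / 10.1 = 4.0 SD above the control mean and (150 − 118) / 10.1 = 3.2 SD above control plus 8. A beta distribution on 0 to 150 with SD 10.1 has skewness −0.31 at mean 110 and −0.45 at mean 118.

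| Assumed scores | Sent to Mann-Whitney |
|---|---|
| Normal | about 10% |
| Bounded beta, both arms at mean 110 | about 17% to 19% |
| Bounded beta, means 110 and 118 | about 22% to 27% over repeat runs |
| Skewness −1 (assumed) | about 76% to 86% |
| Reflected gamma, shape 2, skewness −2/√2 = −1.4 (assumed) | about 97% (35 per arm) |

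The last two rows rest on skewness that appears nowhere in the article.

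**4. What the switch does to error rates.** With no true effect, the rule that tests normality and then chooses rejects in about 5% to 6% of trials in all the scenarios simulated under the null. The t-test alone on scores with skewness −1 rejects in about 5%, so the switch is not needed for validity. At 35 per arm the two tests disagree on p < 0.05 in about 2% to 7% of trials, depending on shape and true effect.

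**The case against.** The mixed model is named only for missing data and not as a rival primary test. It shares the mean-difference target with the t-test. A reader might infer three incompatible analyses, but the text does not support that: one route departs from the sizing target, and only conditionally.

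A reader might also infer that the switch will probably occur because the score is bounded. The protocol's own mean and SD put the bound far away, and the high switch rates need assumed skewness. A further tempting inference is that the analyst could take the smaller of two p-values. The plan does not allow this: the distribution selects the test, and the analysts are masked.

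The rank test also has a real advantage under strong skew. With the shape-2 gamma scores and a true 8-point difference, power at 35 per arm was about 96% for Mann-Whitney and 90% for the t-test. Medians lie on the same 0 to 150 scale, and nothing forbids reporting a mean difference as well.

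Finally, a journal article may leave the normality criterion, model terms and interval to an analysis plan, and the sizing paragraph already points to a t-test.

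These arguments limit the size of the problem but do not remove it. The article is not silent. It states a rule that covers the primary outcome, and that rule can replace the analysis used for sizing. It also names a missing-data method that cannot feed either two-sample test. An analysis plan that followed this text would inherit both faults.

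**Conclusion.** The point holds as a badly fixed primary analysis. As written, a finding of non-normality leaves the primary result as medians and a rank p-value on observed cases, with no mean difference to compare with 8 points. With missing 24 h scores, the plan does not say whether the two-sample test or the mixed model decides.

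The size is moderate. Type I error stays at about 5% to 6%, so the text does not support a claim of serious error inflation. Nor does it show that the missing-data method would go unused, since the article says it will be used; what is absent is its relation to the test. The switch rate is unknown. It is about 10% under normality and about 17% to 27% for a bounded score with the protocol's figures, and higher only under stronger assumed skew. All these rates depend on the assumed Shapiro-Wilk rule. The harm lies in the effect measure and in which analysis decides the trial.

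**What to change.** In section 2.5.4, drop the normality switch for the primary outcome and name one primary analysis, using the method that the plan already cites:

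- Fit a mixed model for repeated measures to QoR-15 at 24 h, 72 h and 1 month with treatment, time and treatment-by-time, in all randomised patients with at least one score.
- Report the 24 h mean difference with its 95% confidence interval, read against 8 points. This result decides the trial.
- Keep the t-test and the Mann-Whitney test on observed 24 h scores as sensitivity analyses.
- Limit the mixed-model sentence to the repeatedly measured scores, QoR-15 and NRS. Measures taken once, such as remifentanil consumption, give it nothing to work with.

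No baseline QoR-15 term is proposed, because Table 1 schedules no preoperative QoR-15. Section 2.5.1 excludes participants who cannot complete the primary outcome. That sentence has to be reconciled with this analysis, or the model would have no missing 24 h scores to handle.

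The cost is a few sentences, and SPSS 23 fits this model. The small downside is more model output to report. Patients with no score at any visit remain outside the model, and the text should say so.
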